## Abstract

**Background:**

Colorectal cancer (CRC) is among the leading causes of cancer-related morbidity and mortality worldwide. Despite clinical practice guidelines to guide surveillance care for those who have completed treatment for this disease as well as screening for first degree relatives of people with CRC, the level of uptake of these recommendations remains uncertain. If outcomes for both patients and their families are to be improved, it is important to establish systematic and cost-effective interventions to improve adherence to guideline recommendations for CRC surveillance and screening.

**Methods/Design:**

A randomized controlled trial will be used to test the effectiveness of a print-based intervention to improve adherence to colonoscopy surveillance among people with CRC and adherence to CRC screening recommendations among their first degree relatives (FDRs). People diagnosed with CRC in the past 10 months will be recruited through a population-based cancer registry. Consenting participants will be asked if their first degree relatives might also be willing to participate in the trial. Information on family history of CRC will be obtained from patients at baseline. Patients and their families will be randomized to either minimal ethical care or the print-based intervention. The print-based intervention for FDRs will be tailored to the participant's level of risk of CRC as determined by the self-reported family history assessment. Follow up data on surveillance and screening participation will be collected from patients and their FDRs respectively at 12, 24 and 36 months' post recruitment. The primary analyses will relate to comparing levels of guideline adherence in usual care group versus print-based group in the patient sample and the FDR sample respectively.

**Discussion:**

Results of this study will provide contribute to the evidence base about effective strategies to a) improve adherence to surveillance recommendation for people with CRC; and b) improve adherence to screening recommendation for FDRs of people with CRC. The use of a population-based cancer registry to access the target population may have significant advantages in increasing the reach of the intervention.

**Trial registration:**

This trial is registered with the Australian and New Zealand Clinical Trials Registry Registration Number (ACTRN): ACTRN12609000628246.

## Background

Colorectal cancer (CRC) is among the most prevalent cancers worldwide and carries a substantial mortality and morbidity burden [1]. Five year survival ranges between 8% and 93%, depending on stage of disease [2]. Among people who have undergone surgical resection for CRC, surveillance colonoscopy is recommended at regular intervals to detect recurrence and metachronous cancers. In Australia, the National Health and Medical Research Council (NHMRC) clinical practice guidelines recommend that colonoscopy is performed at the time of diagnosis, or if this is not possible, within six months' of surgery, and then at an interval of 3-5 years [3]. Although NHMRC guidelines [3] have been available for some time, the level of uptake of the recommendations is uncertain. Australian studies have indicated that between 23%-38% of surveillance colonoscopies are in line with NHMRC recommendations [4,5].

Screening of first degree relatives (FDRs) of patients with colorectal cancer is widely recommended [6]. Evidence for the benefits of screening of first degree relatives of colorectal cancer patients come from prospective and retrospective cohort studies [5,7-9] and from a non-randomized study of relatives in a high risk familial setting, where there was a reduction in mortality from colorectal cancer in those accepting compared to those refusing screening [1]. The type of screening and recommended interval is dependent upon level of risk [3]. Current Australian guidelines classify risk levels for FDRs as shown in Table 1[3]. Recommended screening for each of these risk categories is as follows: *Risk level 1*: Faecal occult blood testing every second year from age 50 years and consider flexible sigmoidoscopy every 5 years. *Risk level 2: *Colonoscopy every 5 years starting at age 50 years or at 10 years younger than the earliest age of first diagnosis of bowel cancer in the family, whichever comes first. Flexible sigmoidoscopy and double contrast barium enema or CT colonography may be offered where colonoscopy is contraindicated. *Risk level 3*: Colonoscopy every one or two years for families with proven Hereditary Non-polyposis Colorectal Cancer (HNPCC) commencing at 25 years or 5 years before the earliest age of cancer diagnosis in the family, whichever comes first; annual screening for proven gene carriers or clinically affected members of Amsterdam-positive families.

**Table 1 T1:** Risk categories for colorectal cancer based on family history

Risk Category	Characteristics
Category 1. At or slightly above average risk	Asymptomatic people who have: • no personal history of bowel cancer, advanced adenoma, or chronic ulcerative colitis, and • either no close relatives with bowel cancer or one first-degree or second-degree relative with bowel cancer diagnosed at age 55 years or older.
Category 2. Moderately increased risk	Asymptomatic people who have: • one first-degree relative with bowel cancer diagnosed before the age of 55 years (without the potentially high-risk features listed below for category 3), or • two first-degree *or *one first- and one second-degree relative(s) on the same side of the family with bowel cancer diagnosed at any age (without the potentially high-risk features listed below for category 3).
Category 3. Potentially high risk	Asymptomatic people who have: • three or more first-degree or a combination of first-degree and second-degree relatives on the same side of the family diagnosed with bowel cancer (suspected HNPCC), or • two or more first-degree or second-degree relatives on the same side of the family diagnosed with bowel cancer, including any of the following high-risk features: - multiple bowel cancers in the one person - bowel cancer before the age of 50 years - at least one relative with cancer of the endometrium, ovary, stomach, small bowel, renal pelvis, ureter, biliary tract or brain, or at least one first-degree relative with a large number of adenomas throughout the large bowel (suspected FAP), or • somebody in the family in whom the presence of a high-risk mutation in the APC (adenomatous polyposis coli) gene or one of the mismatch repair (MMR) genes has been identified.

• The above definitions are based on the National Health and Medical Research Council's clinical practice guidelines [3].

While a small number of studies have attempted to improve adherence to screening among FDRs [10], few studies have evaluated the effectiveness of systematic interventions which target care for both the person with cancer and their FDRs. An improvement in guideline adherence was demonstrated at a single site following dissemination of the guidelines to all specialists and implementation of a nurse co-ordinator role to ensure that screening/surveillance recommendations matched guideline recommendations [4]. However, effective interventions need to be developed that have the potential for broad implementation and that enable follow up and screening advice to be systematically and comprehensively provided to all identified colorectal cancer patients and their relatives, not just to those who present for care. Therefore, the current study will seek to evaluate an intervention which aims to improve screening/surveillance care for both people with bowel cancer and their first degree relatives using a population-based cancer registry as the reliable access point for all such patients. Thus, the study tests an intervention capable of having an impact on the entire affected population [11].

## Aims

The aims of this trial will be to:

i. Test the effectiveness of tailored print-based intervention to improve a) adherence to surveillance colonoscopy recommendations for people with bowel cancer b) adherence to bowel cancer screening guidelines among their first degree relatives.

ii. Examine how the identified cancer patients' and first degree relatives' socio-demographic characteristics, disease characteristics (for index case), risk category (for first degree relatives), intervention groups and providers' characteristics influence whether or not: a) colorectal cancer patients; and b) first degree relatives of colorectal cancer patients, are appropriately screened.

iii. Undertake a cost-effectiveness analysis of the intervention strategy by comparing the differential cost of an intervention and usual care conditions by changes in the quality-adjusted life years associated with each intervention.

## Methods/Design

### Ethics approvals

Full ethical approval for this study has been obtained from the Cancer Council Victoria Human Research Ethics Committee and the University of Newcastle Human Research Ethics Committee.

### Setting

People with a diagnosis of bowel cancer within the last 10 months will be recruited from population-based cancer Victorian Cancer Registry covering the entire Australian state of Victoria (population 5.5 million).

### Patient eligibility and recruitment

People with bowel cancer (index cases) who meet the following criteria will be identified from the cancer registry: 1) aged 18 or older; 2) registered with cancer registry within 10 months of diagnosis. The registry will write to the notifying doctor of each potentially eligible person and ask the doctor to contact the registry within 4 weeks if there is any reason why the patient should not be contacted about the study. Index cases whose doctors perceive them to be unsuitable for the study will be excluded. The registry will contact remaining index cases and ask their permission to pass their contact details onto the research team. Two reminders will be sent to non responders. Those who consent will be invited to participate in the trial with two reminders sent to non responders.

### Assessment of family history

Patients will complete a baseline computer assisted telephone interview (CATI) to assess family history. On the basis of their report of family history each index case and their family will be classified as 1) average risk; 2) increased risk or 3) potentially high risk. These categories, defined according to the definition of the National Health and Medical Research Council (NHMRC), are each associated with different types of screening recommendations. Participants will also complete questions on age, gender, marital status, education and employment, disease characteristics, treatment, screening history, surveillance intentions and quality of life. Quality of life will be assessed using the European Quality of Life Scale (EQ-5D version) which covers 5 dimensions of health: mobility, self-care, usual activities, pain/discomfort and anxiety/depression [12].

### FDR eligibility

First degree relatives of people with bowel cancer will be eligible to participate in the trial if they are a) aged 18 or older; b) English speaking; and c) able to provide informed consent. Those with a prior diagnosis of bowel cancer, Crohn's disease, or inflammatory bowel disease will be ineligible.

### Recruitment of FDRs

Patients will be asked to provide the names and contact details of any living first degree relatives aged 18 or older. They will be asked to indicate which (if any) of their FDRs they are willing for the research team to contact about the study. A choice will be given regarding method of contact of FDRs. Option one will involve the patient being given a letter about the study which they can pass onto their relatives; while option 2 will involve the research team contacting the relative(s) directly by mail. Patients will be asked to seek their relatives' permission prior to selecting the latter option. Non responders for option one receive one reminder letter. The information pack will contain a cover letter, information statement about the study, and ask the person to contact the research team if they were interested in participating. If the index case has provided the relative's phone number, the letter will ask the relative to return a "do not contact" form within the next two weeks if they did not want a researcher to contact them about the study. FDRs that consent to being contacted will be telephoned and asked to participate in a brief screening interview to assess trial eligibility. Consenting eligible FDRs will complete a baseline computer-assisted telephone interview (CATI) which will include questions about age, gender, marital status, education, employment, knowledge about screening and prior screening history and future intentions of screening, use of complementary therapies, and quality of life. Quality of life will be assessed using the European Quality of Life Scale [12].

### Randomization

Consenting patients and their first degree relatives will be randomized as a family unit to either "minimal ethical care" or a tailored print based intervention. Randomization will be conducted centrally using a computer generated procedure. Interviewers will be blind to participants' allocation.

### Intervention

Patients assigned to the intervention group will receive a letter detailing recommendations for follow up care. A fact sheet with information about recommended follow up care will be mailed to patients. The patient's GP and surgeon will also be sent a fact sheet with information about best evidence surveillance care. First degree relatives will receive a tailored letter which provides advice on recommended bowel cancer screening tests and intervals based on their level of family risk. A brochure detailing the three risk levels and their corresponding screening recommendations will be enclosed. Family risk will be determined based on patient self report information and will correspond to the three levels of risk identified in the National Health and Medical Research Guidelines. The GP of the FDR will also receive a tailored letter indicating the likely risk category of the first degree relative. A brochure detailing screening recommendations for each risk category will be enclosed.

### Minimal ethical care

Patients and first degree relatives assigned to the minimal ethical care group will receive a generic booklet on bowel cancer and generic pamphlet on bowel cancer screening respectively. First degree relatives categorized at very high risk will sent the tailored information as per the intervention group as part of our duty of care.

### Follow up assessments

Both first degree relatives and patients will be mailed follow up surveys at 12, 24 and 36 months. First degree relatives will be asked to provide self report information on the type of bowel cancer screening undertaken in the past 12 months (if any), and any days off work due screening. Patients will be asked to provide self report information about participation in surveillance colonoscopy within the past 12 months, quality of life. Patients or first degree relatives who report having had a colonoscopy or bowel cancer screening test in the past 12 months will be asked for permission to contact their doctor to verify the timing and results of the test. A random sample of 10% of self reported screening will be verified in this way to determine accuracy of self reported screening behavior.

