### Sample size

Approximately 3000 eligible new cases of colorectal cancer are expected to be identified through the Victorian Cancer Registry each year. Based on previous experience, 3% of clinicians will refuse permission for their patient to be approached, therefore we expect permission to contact 2900. Based on prior research, we expect 60% of patients contacted by the VCR agree to be contacted by the research team and 70% of these consent to participate in the study. Recruitment will be undertaken for 12 months, thus 1200 index cases will be recruited in total, or 600 per group. *Aim 1*. Assuming that 20% of participants will be lost at each follow-up time (leaving 480, 380, 300 index cases per group available at 12, 24, 36 month), the study will have 80% power, with a 5% significance level, to detect a difference of 10% between experimental groups in the proportion of index cases appropriately surveillance at 12 month follow-up, 12% difference at 24 and 36 month follow-up. It is estimated that there will be an average of 2 eligible first degree relatives for each index case, and that 70% of these will consent and be available for 12 month follow-up, with a 20% loss to follow-up at each of the remaining assessment times. This will provide 1680, 1350 and 1050 relatives at 12, 24 and 36 months. Allowing for a design effect of 2 will provide an effective sample size of 400, 330 and 260 per group at each time point, which is adequate to detect a 10% difference in the proportion of first degree relatives appropriately screened at 12 months, 12% at 24 months and 13% at 36 months with 5% significance level and 80-85% power. A 10% difference at the first follow-up is considered to be clinically meaningful, given the burden of disease from colorectal cancer and the intervention effect is anticipated to increase over time, as the intervention will continue for the three year follow-up period. *Aim 2*. Assuming at least one third of individuals will be appropriately screened at each follow up time, the study will also have at least 80% power to detect differences in characteristics of those who are and are not followed up/screened appropriately of 10-13% for binary variables and 0.2-0.25 standard deviations for continuous variables for index cases, and 11-14% for binary variables and 0.22 -0.27 standard deviations for continuous variables for FDRs.

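### Follow-up as described gives no route to the outcomes of survey non-responders, and the 12-month look-back loses tests from a missed year, so the 24- and 36-month comparisons are open to response bias

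*Protocol article*

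**What the plan says.** Under Follow up assessments, patients and relatives are mailed surveys at 12, 24 and 36 months. Patients give "self report information about participation in surveillance colonoscopy within the past 12 months, quality of life"; relatives report the screening tests they had over the same look-back. Those who report a colonoscopy or screening test "will be asked for permission to contact their doctor to verify the timing and results of the test", and a random 10% of reported tests is verified to assess the accuracy of self-report. The article describes no other source for the adherence outcome.

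Under Sample size, the starting point is given as "thus 1200 index cases will be recruited in total, or 600 per group", and the plan assumes "20% of participants will be lost at each follow-up time (leaving 480, 380, 300 index cases per group available at 12, 24, 36 month"). The detectable effect for index cases at the later waves is a "12% difference at 24 and 36 month follow-up". For relatives, the expected numbers are 1680, 1350 and 1050 at the three waves. The same section expects the intervention effect to grow over time.

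Under Statistical analysis, the Aim 1 comparison is a chi-square test of the proportions adherent in each arm.

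**The concern.** There are two separate problems.

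**Non-responders.** Doctor access is tied to a returned survey that reports a test. Someone who returns no survey is never asked, so under the rule as written no adherence outcome can be obtained for that person elsewhere. Returning a survey about bowel tests is plausibly related to having had one. That relation could also differ by arm: intervention families receive letters recommending specific care, and their doctors are written to, while most controls receive generic material. Equal overall retention would not reveal such a difference. The exposure is greatest at 24 and 36 months, when the most outcomes are missing and the largest effect is anticipated. An analysis plan can specify bounds or imputation, but it cannot supply outcomes that nobody had permission to collect.

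**Look-back.** Someone who misses the 12-month survey and returns the 24-month one is asked only about the past 12 months. A test in the missed year is not recorded, although it may still count at 24 months.

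**Working it through.** **1. The plan's own attrition figures.** Inputs: 600 index cases per group and 20% loss at each wave (Sample size).

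- Compounded: 600 × 0.8 = 480; 600 × 0.8² = 384; 600 × 0.8³ = 307. The plan states 480, 380 and 300, so its figures are reproduced with rounding.
- Loss by 36 months: 1 − 300/600 = 50% on the stated counts, or 1 − 0.8³ = 48.8% on the stated rate.
- Relatives, 12 to 36 months: 1 − 1050/1680 = 37.5%. Loss before 12 months cannot be separated out, because the plan's 70% combines consent with availability at 12 months.

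**2. Power is not the problem.** With 300 per group, a 12-point difference and a two-sided 5% test, power is 0.90 at a control rate of 23%, 0.86 at 33.3%, 0.84 at 38% and 0.84 at 44%. The article states no Aim 1 control rate. This range spans its Background figure ("between 23%-38% of surveillance colonoscopies are in line with NHMRC recommendations"), its Aim 2 assumption of at least one third, and a value near the worst case for variance. The stated 80% is met.

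**3. Illustration of bias.** Inputs from the plan: about 50% retained and 300 per group at 36 months. Assumptions not in the documents: no true effect, true adherence p = 0.33 in both arms, and the response patterns below. If the adherent respond with probability a and the non-adherent with probability b, the rate among responders is

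p·a / [p·a + (1 − p)·b].

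- a = b = 0.50: 0.33.
- a = 0.55, b = 0.475: 0.1815 / (0.1815 + 0.31825) = 0.363.
- a = 0.60, b = 0.45: 0.198 / (0.198 + 0.3015) = 0.396.

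Each pattern retains about 50% overall, so the arms would look balanced on retention.

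| Intervention (a/b) | Control (a/b) | Observed rates | Spurious difference | Test rejects, 300 per group |
|---|---|---|---|---|
| same as control | same as intervention | equal | 0 | about 5% |
| 55% / 47.5% | 50% / 50% | 36.3% v 33% | 3.3 points | about 13% |
| 60% / 45% | 55% / 47.5% | 39.6% v 36.3% | 3.3 points | about 13% |
| 60% / 45% | 50% / 50% | 39.6% v 33% | 6.6 points | about 39% |

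The adherence rate matters little. If adherent intervention patients respond 1.25 times as often as the non-adherent, and control response is unrelated to adherence, the spurious difference is 4 to 6 points for true rates of 23% to 44%, and the test rejects 22% to 28% of the time.

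**4. What the data alone allow.** With half the outcomes missing in each arm and an observed difference of +12 points, the all-randomised difference is 0.5 × 12 = 6 points plus a missing-half contribution between −50 and +50. The bounds are therefore −44 to +56 points. These extremes are not plausible values; they show how much rests on the assumption about non-responders.

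**5. Look-back.** The Background gives category 1 relatives a two-year interval for faecal occult blood testing and category 2 relatives a five-year interval for colonoscopy. Take a category 1 relative tested at month 6 who misses the 12-month survey and returns the 24-month one. The returned survey covers roughly months 12 to 24. The test, 18 months old, lies inside the two-year interval but outside the question. The article does not give the scoring rule, but no rule that counts earlier tests can use one that was never recorded.

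**The case against.** The strongest reply is that this is a condensed article. The baseline consent content is not shown, and reminders, telephone follow-up, death linkage or a further outcome source may sit in the full protocol. That is fair for anything on which the article is silent. It carries less weight for the doctor-access rule, because the article states who is asked, and non-responders are not among them.

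A reader might infer three stronger claims that the documents do not support:

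- **That collection stops at a missed survey.** Nothing says mailing at 24 or 36 months depends on an earlier reply. The look-back problem in fact assumes that mailing continues.
- **That the later comparisons cannot be checked at all.** Baseline interviews record screening history, intentions and demographics, and many people lost later will have answered at 12 months. Responders and non-responders can be compared by arm on these, and an unseen analysis plan may specify bounds or imputation. What remains unknown is whether non-responders were tested.
- **That half of index cases are survey non-responders, or that a bias of 6.6 points is expected.** Some of the loss will be deaths, and the share is not given. The response patterns are assumed; no text supports a particular asymmetry, both arms receive printed material, and if the arms respond alike the bias under no effect is zero.

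It is also fair that the look-back loss affects only intermittent responders, whose number the plan does not give, and that recruitment began in 2010, so a new baseline item cannot reach everyone.

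**Conclusion.** The concern holds in limited form. As described, outcomes of survey non-responders cannot be obtained from their doctors, while the plan expects about half of index cases to be unavailable by 36 months and relatives to fall by 37.5% between 12 and 36 months. If response depends on adherence differently by arm, the 24- and 36-month comparisons are biased, and the available data allow only a partial check. Under the assumed patterns, the spurious difference ranges from 0 to about 3 to 7 points against a 12-point target. This shows what modest asymmetry could do; it does not forecast what will happen. The look-back loss is a separate, smaller defect of unknown size. Both are worth correcting because the changes are cheap and later analysis cannot replace data that were not collected.

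**What to change.** 1. Word each follow-up survey to ask for bowel tests and their dates since the last survey the participant returned, or since recruitment if none was returned. This costs a wording change and somewhat longer recall.
2. At the baseline interview, ask participants not yet interviewed for permission to contact their doctor about bowel tests during follow-up, whether or not surveys come back. Ask those already recruited at the next contact, accepting that this will be incomplete because the least responsive are the least likely to reply. This costs one consent item and one letter.
3. Direct part of the existing verification effort to a random sample of consenting non-responders in each arm. Use their adherence to set the missing-outcome assumption in a sensitivity analysis of the 24- and 36-month comparisons. Those who consent may themselves differ from those who do not, so this narrows the uncertainty without removing it.

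The main downside is that fewer positive self-reports are verified, which makes the estimate of self-report accuracy less precise.
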